### Study objectives

#### Objective 1

To investigate how the transition to independent sitting changes infants’ visual attention to faces and toys during free play.

Prediction: Due to fewer postural constraints and less effort to maintain balance, infants, after learning to sit independently, would look longer at the caregiver’s face and toys than before acquiring this motor milestone [15, 17]. However, during the phase transition (attempting-sitting), infants’ look less toward faces and toys would be shorter than before and after the acquisition of sitting due to difficulties in maintaining a stable body position.

#### Objective 2

To investigate how the transition to independent sitting influences infants’ visual attention to mouth in a screen-based eye-tracking task.

Prediction: Increasing experience with viewing faces in an upright orientation, infants’ visual attention to the mouth while watching talking faces in a free-viewing task gradually increases as they gain sitting proficiency.

#### Objective 3

To investigate how the transition to independent sitting associates with infants’ vocal production.

Prediction: After learning how to sit independently, infants vocalize more and produce more advanced vocalizations (such as canonical babbling) than before acquiring this motor milestone [53, 54]. However, during the transitional phase (attempting-sitting), infants vocalize less due to difficulty in allocating attention to multiple tasks during the acquisition of a novel skill [50].

### Methods and analysis

#### Sampling plan

Participants are recruited through snowballing, using ads on social media (Facebook, Instagram) and parenting blogs in Poland. The participants are recruited from the metropolitan area of Warsaw (a city with over 1.8 mln inhabitants). We expect the majority of participants to come from families with a middle-class background and mean-to-high socio-economic status – we will collect SES-related information during the first visit. For their participation, infants receive a diploma and a small gift (a baby book). Infants’ caregivers provide written informed consent before data collection. This study has been approved by the Research Ethics Committee at the Institute of Psychology, Polish Academy of Sciences.

### Sample size

GPower analysis indicates that based on the standard repeated-measures design for a moderate effect size, a minimum sufficient number of participants should be ≈ 30. We aim to recruit 60 infants to overcome the attrition rate and missing data, which are common issues in infant studies (e.g [55]).

### Study design

Our project follows a milestones-based longitudinal experimental design in which infants are invited to the lab around the time they approach the transition to independent sitting. We use a milestone-based approach (e.g [37])., rather than an age-range approach to account for large individual differences in the timing of motor milestone acquisition. Parents fill in weekly surveys about the gross motor development of their infants (illustrated item list for pre-screening if anything has changed in the past week), and these answers are used to schedule lab visits. Furthermore, during each lab visit, infants’ stage of sitting acquisition will be confirmed using two approaches. First, we will use the standardized assessment, following the Alberta Infant Motor Scale [56] to measure the infants’ *capacity* to sit alone. Second, we will measure their *performance*, so the actual time spent by infants in a sitting position during infant-parent interactions by applying the posture classification algorithm based on IMU data [57], recorded during lab visits.

Furthermore, infants’ ages will be added to the analyses to control for the interaction between age-related and motor-milestone-related effects.

Each infant will participate in 3 or 4 visits (depending on the individual development with respect to independent sitting):

pre-sitting (1 visit): when an infant stays comfortably in prone while one hand is free for manipulating objects.attempting-sitting: transition to independent sitting (1 or 2 visits, depending on the progress of the acquisition of sitting) when an infant is able to sit with support while maintaining the head in the midline; an infant can also attempt the position of brief independent sitting without arm support but cannot be left alone in sitting position (first unstable attempts of independent sitting).expert-sitting (1 visit): an infant can comfortably sit independently without any support, can be left alone in sitting, and play with toys in this position.

The above-mentioned definitions are based on the Alberta Infant Motor Scale [56].

### General procedure

During each lab visit, interactions will be recorded in an infant-friendly laboratory room on a carpeted play area. Upon the family’s arrival, an experimenter will explain the study protocol and obtain informed parental consent. Once the infant is familiarized with the laboratory, a screen-based eye-tracking task will start (see detailed procedure below). After the screen-based eye-tracking task, the wearable motion trackers will be put on the infant (on arms and legs) and caregiver (on arms), and a wearable eye-tracker will be positioned on the infant’s head. Then, a set of parent-child interaction tasks with different sets of age-appropriate toys will take place. The caregivers will not receive any instructions other than to play with their children as they typically would do at home. To investigate the cross-situational stability of effects, there will be 4 different interactive tasks during each meeting: book-sharing, rattle-shaking, playing with manipulative toys, and playing with toys that are aimed at eliciting parental action demonstration, each lasting around 5 min (see detailed description below). The order of plays will be randomized between participants and testing sessions. Then, there will be a free-play task without wearable motion trackers and wearable eye-tracker. All tasks will be recorded using 3 remote-controlled HD CCTV cameras (Axis), and the sound recording synchronized with the video for vocal production analysis will be carried out with a high-grade cardioid membrane condenser microphone (Sennheiser e914) placed underneath one of the cameras. Finally, a standardized assessment of gross motor development will be conducted, following the Alberta Infant Motor Scale [56]. Additionally, the caregivers will fill out several questionnaires and answer questions related to demography and socioeconomic status (see **Control Variables** section for an overview).

### Interactive tasks

**Rattle-shaking**: duration of approximately 5 min; the infant and the parent were given two maracas rattles and two small and light barbell rattles.**Book-sharing**: duration of approximately 5 min; the infant and the parent were given two small baby books and one small book with tactile elements.**Playing with small manipulative toys (infant object exploration)**: duration of approximately 5 min; the infant and the parent were given a sensory pop-it toy, a sensory toy with propellers that spin down a corkscrew pole, a wooden wiggly worm and a sensory bee toy with different silicone elements.**Playing with larger manipulative toys (parental action demonstration)**: duration of approximately 5 min; the infant and the parent were given a set of toys that provided multimodal feedback (sounds, movements) and were designed for older children, so infants needed parental action demonstration: a silicone-pulling toy with textured cords, a spinning toy with small balls inside, a sensory-exploration toy with elements with different textures that can be pushed, spun or clicked and make different sounds, a roll-along pull toy telephone with a smiling face that makes chattering sound and the eyes move up and down when pulled.**Free Play (without wearables)**: duration of approximately 5 min; the infant and the parent were given toys encouraging open play: a set of stacking cups, a wooden box with a drawer and a wooden ball, a rattle, a set of 4 plastic flowers that swing freely on the lightweight ring, a small finger puppet book, and a small cloth book with crinkle fabric and animal tails with different textures.

### Objective 1. To investigate how the transition to independent sitting changes infants’ visual attention to faces and toys during free play

#### Mobile eye-tracking procedure

The experimenter will put the wearable eye-tracker Pupil Labs Neon with a “Ready Set Go frame” on the infant’s head (**see** Fig. 1). The binocular eye-tracking is based on real-time neural network technology. The eye-tracking process relies on two infrared eye cameras recording at 200 Hz and one scene camera recording at 30 Hz and does not require calibration. The device also includes an Inertial Motion Unit with an accelerometer, magnetometer, and gyroscope. Initial pilot data collection showed great tolerability by infants. The experimenters will position the eye-tracker on the infant’s head so that the eye cameras are pointing toward the eyes and the scene camera is directly above the eyes and centered. Once the eye-tracking equipment is properly set up, the dyads will participate in 4 types of play activities (see **General procedure** section). After the session, the recordings will be saved for further analysis.

#### Mobile eye-tracking data analysis - visual attention to faces

To assess developmental changes in infants’ visual attention to faces during play with caregivers, we will automatically analyze the data from the mobile eye-tracking and the infant’s first-person video of the scene. In the first step, the % of recording duration when the caregiver’s face is visible in the infant scene will be examined using an artificial intelligence (AI) face detector. We plan to use RetinaFace [58], but since research in this area is developing at a very high pace, we will review the available options regularly.

We will map gaze data onto faces that appear in the visual scene. Then, we will analyze the percentage of recording duration where fixations on faces occur. Moreover, we will extract the percentage of time the infant fixated on faces out of the time when the faces were detected in the infant scene camera (so if the face is visible in the field of view, whether the infant looks at it).

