### The current study

The acquisition of independent sitting transforms infant visual attention to faces [12, 15] in general but it is not clear whether it also contributes to the increase in visual attention to the mouth area as a source of audiovisual speech cues. The second related but unexplored issue concerns how the acquisition of sitting may alter the allocation of attention to speaking faces relative to other attractive visual objects during free-flowing social interactions. The proposed study, for the first time, combines the measurement of visual attention in a screen-based task with the measurement of attention during free-flowing social interaction in a design that tests their dependence on sitting acquisition. The acquisition of sitting potentially reorganizes multiple aspects of speech and face processing [52].

We aim to examine developmental trajectories in a cohort of infants with a low likelihood of ASD first to determine whether changes in vocal production and visual attention to faces occur simultaneously in relation to the acquisition of independent sitting. Understanding these trajectories first in typically developing infants will allow us to establish a baseline prior to any studies with EL-infants.

Pilot data collection and finalization of the study design were conducted between 13.07.2023 and 09.02.2024. The recruitment and data collection are ongoing. Data collection started on 16.02.2024. The data analysis has not started. The expected completion date of the recruitment is the end of August 2025.

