#### Mobile eye-tracking data analysis - visual attention to toys

To assess developmental changes in infants’ visual attention to toys during play with caregivers, the infant’s first-person video of the scene with overlaid fixation data will be downloaded for further annotations. Infants’ visual attention will be then manually annotated using ELAN software (https://archive.mpi.nl/tla/elan). Trained coders will label the segments based on the crosshair’s location, indicating whether the infant looked at any of the toys (each toy will be considered a separate Area-of-Interest (AOI). Coders will also annotate moments when the object of fixation cannot be readily discerned. Furthermore, coders will also exclude moments when the eye-tracker was being adjusted after being bumped or moved by the infant.

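### Face-looking is divided by whole recording time rather than valid-gaze time, so gaze loss or tracker adjustment that differs by sitting stage would read as a change in face attention

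*Protocol article*

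**What the plan says.** Under the heading on mobile eye-tracking analysis of visual attention to faces, the pipeline is automatic: "we will automatically analyze the data from the mobile eye-tracking and the infant’s first-person video of the scene". Two gaze-based outcomes follow. For the first, "we will analyze the percentage of recording duration where fixations on faces occur". The second is the "percentage of time the infant fixated on faces out of the time when the faces were detected in the infant scene camera". No step in that section removes time without valid gaze, or time when the device was being repositioned, from either denominator.

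The next section, on toys, uses the same first-person recordings but hand coding. There, "coders will also exclude moments when the eye-tracker was being adjusted after being bumped or moved by the infant". Unclear gaze is handled differently: "Coders will also annotate moments when the object of fixation cannot be readily discerned". The text does not say that these annotated moments are then dropped. It describes the labelling of looks at toys and states no denominator for a toy percentage.

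Objective 1 predicts that looks at faces and toys will be shorter during attempting-sitting than before or after it, because the infant has trouble balancing. The Statistical analyses section fits a linear mixed model for the effect of sitting expertise on each outcome, with age added.

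**The concern.** When the denominator is the whole recording, every second without usable gaze enters as a second not spent looking at the face. The observed share then mixes two things: what the infant looked at, and how often the device could tell. The second may well change with motor stage. The protocol itself expects infants to bump or move the tracker, and an infant who is struggling to stay upright could plausibly lose gaze more often.

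What is at stake is the main Objective 1 contrast. The predicted dip at attempting-sitting is attributed to postural instability, and gaze loss caused by that same instability would produce a dip of the same sign with no change in attention. Adjusting for age does not separate the two.

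The protocol recognises adjustment time as unusable in the toy section, yet states its removal only there. For Objective 2 it divides mouth and eye looking by looking time to the face, a denominator made of recorded gaze. The mobile face measure has no such protection.

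**Working it through.** The plan gives no figure to reproduce here, and no rate of gaze loss by stage. All rates below are assumptions chosen to show the range.

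**Inputs**
- Denominator of the first face measure: recording duration (face section).
- Denominator of the second: time with a face detected (face section).
- Exclusion of adjustment time: stated for toy coding only (toy section).
- True face share of valid gaze: assumed 15%, the same at every stage.
- Loss L (gaze loss plus adjustment time, as a fraction of the recording): assumed 10% to 40%, unrelated to where the infant is looking.

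**First face measure**

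Observed share = true share × (1 − L). With valid-gaze time as denominator, the factor (1 − L) cancels and the share stays at 15%.

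| Assumed loss, pre / attempting / expert | Reads as, with recording duration | Attempting versus pre | Expert versus pre |
|---|---|---|---|
| 10% / 10% / 10% | 13.5% / 13.5% / 13.5% | 0 | 0 |
| 10% / 20% / 10% | 13.5% / 12.0% / 13.5% | −11% | 0 |
| 10% / 30% / 10% | 13.5% / 10.5% / 13.5% | −22% | 0 |
| 20% / 40% / 15% | 12.0% / 9.0% / 12.75% | −25% | +6% |
| 30% / 20% / 10% | 10.5% / 12.0% / 13.5% | +14% | +29% |

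For example, in the third row 0.15 × 0.90 = 13.5%, 0.15 × 0.70 = 10.5%, and 10.5/13.5 − 1 = −22%. The relative change depends only on the loss rates, not on the assumed 15%. In the last row, loss falls as infants mature and the artefact is a steady rise.

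**Second face measure**

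Assume a face is in view 40% of the time, so the true conditional share is 0.15/0.40 = 37.5%. Face-in-view time includes time without gaze, so the observed value is 0.15 × (1 − L)/0.40.
- L = 10%: 0.135/0.40 = 33.8%.
- L = 30%: 0.105/0.40 = 26.3%.

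The relative fall is again 22%. Conditioning on face visibility does not remove the problem.

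**How far the toy measure differs**

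Assume equal true shares of 20% for face and toys, adjustment time 10% and unreadable time 20% of the recording.
- Face over the whole recording: 0.20 × 0.70 = 14.0%.
- Toy with only adjustment time removed, the one exclusion the text states: 0.14/0.90 = 15.6%.
- Toy with unreadable time removed as well, which the text does not state: 0.14/0.70 = 20.0%.

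The gap that the text itself supports is the smaller one, 14.0% against 15.6%, and it presumes that the unstated toy denominator is recording time minus adjustment time.

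**The case against.** The strongest reply is that this is a condensed article. Rules for valid samples usually sit in a fuller document, both streams come from the same recordings, and nothing prevents the coders' exclusions from being applied to faces too. That would settle the matter if the article were silent. It is not silent on the denominator: it names recording duration and face-detected time, and it places the adjustment exclusion under toys only.

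The second reply is that differing loss by stage is assumed. This stands. The article reports that pilot infants tolerated the device well and gives no loss rates. With equal loss there is no spurious change, so the bias is conditional.

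The third is that valid-gaze time is not automatically unbiased. This also stands. Suppose loss is 10% while the infant looks at the face and 30% otherwise. A true 15% share then reads 0.135/(0.135 + 0.85 × 0.70) = 0.135/0.730 = 18.5% over valid gaze, against 13.5% over the recording. The replacement rests on loss being unrelated to gaze target.

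Three stronger readings are tempting and should not be drawn:
- *Toy-looking drops all unreadable time, so the two shares cannot be compared.* Unclear moments are annotated, not stated to be excluded, and the toy denominator is not given. The mismatch is firm for adjustment time only, and a common denominator can be built from the same recordings.
- *A planned face-versus-toy test is broken.* The introduction asks how sitting may "alter the allocation of attention to speaking faces relative to other attractive visual objects", but each outcome is modelled separately and no direct comparison is specified.
- *Toy faces will be double counted.* The article does say "We will map gaze data onto faces that appear in the visual scene", and one toy is "a roll-along pull toy telephone with a smiling face". But the preceding step refers to the caregiver's face, and nothing shows that the detector would register a painted one.

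**Conclusion.** The concern holds for the face outcomes as defined. Both gaze-based face percentages use denominators that include time when gaze could not be measured, so they fall in proportion to gaze loss. This needs no comparison with toys.

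Whether a false stage effect arises depends on loss differing between stages, which is plausible but undocumented. Under the assumed rates, the attempting-sitting visit would show a spurious relative change of −11% to −25% against pre-sitting, or +14% if loss falls with maturity. Under equal loss the change is zero. The direction of greatest concern is a dip at attempting-sitting, because it coincides with the prediction and could not be told apart from it. The first-step measure, the share of the recording in which the caregiver's face is visible, uses no gaze data and is not affected by gaze loss.

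This should be settled before analysis begins. A denominator changed after the results are seen would be open to the charge of selection.

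**What to change.** 1. Define valid-gaze time as recording time minus tracker-adjustment intervals and minus samples without gaze. Use it as the denominator for both face and toy percentages, and state the toy denominator.
2. For the conditional face measure, use valid-gaze time with the caregiver's face in view.
3. Apply the coders' adjustment intervals to the automatic face stream as well as the toy stream. State one rule for moments when the fixated object is unclear, and use it in both.
4. Say that only the caregiver's face counts as a face.
5. Report the valid-gaze percentage by sitting stage, so that readers can see whether loss differs.
6. Keep the recording-duration version as a sensitivity analysis, because the new denominator assumes that loss is unrelated to gaze target. If the two versions disagree on the stage effect, report both.

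The cost is a modest amount of extra processing. The adjustment intervals and unclear moments are already to be coded for the toy analysis, no new data are needed, and the article states that data analysis has not started.

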#### Mobile eye-tracking data analysis - visual attention to toys

To assess developmental changes in infants’ visual attention to toys during play with caregivers, the infant’s first-person video of the scene with overlaid fixation data will be downloaded for further annotations. Infants’ visual attention will be then manually annotated using ELAN software (https://archive.mpi.nl/tla/elan). Trained coders will label the segments based on the crosshair’s location, indicating whether the infant looked at any of the toys (each toy will be considered a separate Area-of-Interest (AOI). Coders will also annotate moments when the object of fixation cannot be readily discerned. Furthermore, coders will also exclude moments when the eye-tracker was being adjusted after being bumped or moved by the infant.

**Fig. 1 Fig1:**
[figure not shown]
Positioning of the wearable eye-tracker on an infant’s head (left) and an example frame from the eye-tracking recording (right). The images are displayed with permission from the caregiver

### Objective 2. To investigate how the transition to independent sitting influences infants’ visual attention to mouth in a screen-based eye-tracking task

#### Screen-based eye-tracking procedure

The eye-tracking task is the first task during each visit (after the period of getting familiar with the testing room). During the eye-tracking task, infants will sit on their caregiver’s lap approximately 60 cm from the monitor presenting stimuli. The eye-tracking data will be collected on a Gazepoint GP3 eye-tracker recording at 60 Hz. The stimuli will be presented on the 23.8” monitor (1920 × 1080 pixels, 75 Hz refresh rate) using PsychoPy software (version 2021.1.4 [59], running on a laptop with Windows 11 operating system. The standard 5-point calibration procedure will be conducted at the beginning of each eye-tracking session using Gazepoint software (as recommended by the manufacturer). We will use the eye-tracking data if 4 or 5 points were successfully calibrated.

The stimuli consist of 9 videos of actresses (1 actress per video) articulating infant-friendly stories and nursery rhymes presented in a fully randomized order (mean duration of each clip = 30.4 s). In all clips, the speaker’s head is centered in the video, providing a full frontal view of the face on a black background (see Fig. 2 for an example). Each video is preceded by a moving picture accompanied by a sound (attention-getter) to focus the infant’s attention on the center of the screen (the approximate location of the actress’s nose). When an infant looks at the attention-getter, the experimenter starts the next trial (max. display time of each attention-getter is 2 s). In total, the entire eye-tracking procedure lasts around 5 min.

